### Blood sampling and processing

A fasting blood sample was taken by a qualified phlebotomist, using a sterile Vacutainer Flashback needle and needle holder between 7.00 am and 10.00 am to avoid any diurnal variation, or the effects of recently eaten food on the indices measured. Subjects fasted (no food or beverages, excluding water) for 12 hours prior to this blood sample. Four millilitres of blood was collected into an EDTA tube and refrigerated at 4°C before being sent to Diagnostic MedLab for analysis of haemoglobin. Blood (3.5 mL) was collected into a SST tube for the analysis of serum ferritin and CRP and 10 ml of blood was collected into a red top tube for the analysis of soluble transferrin receptor and carotenoids. Both of these vacutainers were kept at ambient temperature for 30 minutes to allow time to clot, and then centrifuged for 10 minutes at 2500 g at 4°C within 2 hours. Six millilitres of blood was collected into an EDTA tube for the analysis of ascorbic acid. All tubes were protected from light post collection. The EDTA tube was centrifuged immediately at 2500 g at 4°C. This was separated without delay and 450 μL of the sample was mixed with 450 μL 10% trichloroacetic acid using a vortex mixer. Aliquots of serum were placed in 1.5 mL Nalgene System 100 cryogenic vials, immediately frozen on dry ice, protected from light and stored within 2 hours of collection at -80°C whilst awaiting analysis [25]. Samples collected at baseline and the end of the study for each subject were analysed in the same assay run to eliminate inter assay variability.

### Biochemical analysis

Details of methods and analysis are shown in Table 2.

**Table 2 T2:** Biochemical analysis

Measure	Place of analysis	Method
**Blood analysis**		

Serum ferritin	Diagnostic Medlab, Auckland	Immunoturbidimetric test (Roche Diagnostics, Indianapolis) (Cat. No. 11661400)

Serum C-Reactive Protein	Diagnostic Medlab, Auckland	Particle enhanced immunoturbidimetric assay (Roche Diagnostics, Indianapolis) (Cat. No. 03002039)

Haemoglobin	Diagnostic Medlab, Auckland	SLS-Hb (sodium lauryl sulphate-Hb) method using automated haematology analyser XE-2100 (Sysmex Corporation, Auckland, NZ)

Soluble transferrin receptor	LabPlus, Auckland	Latex bound anti-sTfR antibodies react with antigen in sample to form antigen/antibody complex. Following agglutination measured turbidimetrically at 570 nm

Ascorbic acid	LabPlus, Auckland	Fe^3+ ^ions added to ascorbate which is oxidised to dehydroascorbate. Fe^2+ ^ions produced are measured by complexing them with ferrozine, the absorbance of the coloured complex is read at 560 nm. FeCl_3 _is added and incubation continued for 5 minutes. Concentration of ascorbate in specimen after suitable blank correction is proportional to change in absorbance over 5 minute period.

Carotenoids (Retinol, Alpha- & Gamma-Tocopherol; Lutein/Zeaxanthin, Lycopene, Alpha- & Beta-Carotene, Beta-Cryptoxanthin	Department of Medicine, University of Melbourne	HPLC method C18 column with absorbance detection at 292 nm for the tocopherols, 325 nm for retinol and 450 nm for carotenoids.

### Anthropometric measurements

Height, weight, waist and hip circumferences were measured in duplicate by a trained researcher using the International Society for the Advancement of Kinanthropometry (ISAK) protocol and standards. Quetelet's Body Mass Index (BMI) was calculated from height and weight.

### Questionnaires

At the first visit, subjects completed a face to face interview with a researcher regarding demographic and biographic information. This included questions on age, ethnicity; lifestyle questions (e.g. smoking) and eating patterns (e.g. vegetarian diets). A medical history was obtained from each subject which included questions regarding previous diagnosis or treatment for iron deficiency, blood loss, medication and supplement use in the past year.

At both visits, physical activity was measured using the validated New Zealand Physical Activity Questionnaire Short Form (NZPAQ-SF) [26]. Subjects were asked about the number of days and time spent brisk walking, or involved in moderate and vigorous physical activity over the past week.

Subjects completed two online questionnaires at baseline and end. The first questionnaire was a food frequency questionnaire (FFQ) which included iron containing foods and foods known to affect iron absorption. This was developed to determine overall dietary intake over the past month and to assess any changes in intake between groups over the course of the study. The FFQ was part of a computerised iron habits assessment tool (CIHAT) developed by the researchers [27] and is currently being assessed for its validity and reproducibility.

The second questionnaire asked about blood loss using a previously validated questionnaire [28]. This questionnaire was updated to include details on sanitary items (brand and absorbency) so that subjects could select the sanitary item that they used.

### The breakfast

Each breakfast consisted of 64 g breakfast cereal provided in a sealed individual packet, 150 ml milk and either a banana or two ZESPRI^® ^GOLD kiwifruit. The cereal was developed by food technologists at Hubbard Foods Ltd, Mangere, Auckland, NZ. Ferrous sulphate (Zenica BioPlus Pty Ltd, Australia) was added to a wheat flake cereal with apricot pieces to provide 16 mg iron per serve. Long Life Slim low-fat 0.1% ultra heat treated milk (Pams, New Zealand) was provided to eat with the cereal. ZESPRI^® ^GOLD kiwifruit stored at 1°C were provided by ZESPRI^® ^International Ltd. Bananas were sourced that were of similar size (approximately 100 g) and purchased in various stages of ripeness from market gardeners (MG Marketing, Auckland, NZ).

The breakfast cereal and milk were homogenised and analysed for their nutrient content at the end of the study (see Table 3). Ten packets of breakfast cereal and 3 one-L cartons of milk were sent to each venue from which a composite sample was obtained. Samples of kiwifruit and bananas were stored every two weeks at -80°C and protected from light. These were analysed at the end of the study. Each nutrition laboratory received bananas that were stored throughout the 16 week period. Two batches of kiwifruit were sent to each nutrition laboratory for analysis. The first batch consisted of three whole kiwifruit stored over the first six weeks of the study. The second batch consisted of three whole kiwifruit stored over the final six weeks of the study.

**Table 3 T3:** Nutrient analysis

Nutrient	Place of analysis	Method of analysis
Gross energy (kJ)	Nutrition Lab, Massey University, Palmerston North	Bomb calorimetry

Moisture	Nutrition Lab, Massey University, Palmerston North	Moisture: Convection oven 105°C, AOAC 930.15, 925.10

Protein (g)	Nutrition Lab, Massey University, Palmerston North	Leco, total combustion method. AOAC 968.06

Ash	Nutrition Lab, Massey University, Palmerston North	Furnace 550°C, AOAC 942.05.

Fat - total (g)	Nutrition Lab, Massey University, Palmerston North	Fat: Acid hydrolysis/Mojonnier extraction. AOAC 954.02 (milk and cereal) Fat: Soxtec extraction, AOAC 991.36

Carbohydrate (total) (g)	Nutrition Lab, Massey University, Palmerston North	Calculation by difference

Dietary fibre (g)	Nutrition Lab, Massey University, Palmerston North	Enzymatic-gravimetric method. AOAC 991.43

Iron (mg), Calcium (mg), Copper (mg), Phosphorus (mg) & Zinc (mg)	Asure Quality, Auckland	Plasma emission spectrometry

Ascorbic acid (mg)	Nutrition Lab, Massey University, Palmerston North	HPLC

Vitamin A (as retinol) (μg)	Nutrition Lab, Massey University, Palmerston North	As Retinol, HPLC, AOAC 974.29 (4)

Lutein + zeaxanthin (μg), Beta-carotene (μg), Alpha-carotene (μg)	Plant and Food Research, Auckland	HPLC

Citric acid (mg)	Asure Quality, Auckland	Boehringerr Mannheim test kit (via titration)

Polyphenols (mg)	Plant and Food Research, Auckland	HPLC (sum of all peaks detected at 280 nm) with identification of specific compounds when possible

Phytic acid (mg)	Nutrition Lab, Massey University, Palmerston North	Megazyme kit, Megazyme International Ireland Ltd

Food samples (twenty random samples per product) were weighed for each product. Samples of cereal were taken from 4 separate cartons, banana from 1 weeks supply and kiwifruit across four separate deliveries. The mean (SD) weight of the cereal was 64.4 (3.7)g, peeled bananas weighed 104.1 (14.3)g, and one peeled kiwifruit weighed 85.4 (4.3)g.

Food composition data from ZESPRI^® ^International Ltd indicate that two ZESPRI^® ^GOLD kiwifruit (170.8 g) provided 186.0 mg ascorbic acid, 525.9 μg lutein and zeaxanthin, 6.0 μg of alpha carotene and 0 μg of beta carotene [21]. One banana (104.1 g) provided 9.1 mg ascorbic acid, 22.9 μg lutein and zeaxanthin, 26.0 μg of alpha carotene and 27.1 μg of beta carotene [29].

The breakfast cereal and milk were provided at the first visit and this was used as an opportunity to educate the subjects about the breakfast. The nutritional composition of the breakfast was explained. Subjects were asked to shake their packet of cereal before opening to ensure the iron was evenly mixed, and instructed to add 150 ml of milk to their cereal using the measuring jug provided. They were asked to eat the banana and kiwifruit with, immediately before or immediately after consuming the breakfast cereal. They were asked not to consume any other food or fluids (apart from tap water) with or one hour either side of consuming the breakfast. Instructions were given for eating the banana and the kiwifruit. Subjects were asked to discard the skin of the kiwifruit and to eat as much of the flesh as possible. It was emphasised that it was important to eat all of the cereal, milk, and fruit. The reasons for the instructions were individually explained to each subject, and also explained in a booklet that each subject was given to take home.

Subjects were provided with 120 packets of cereal and 17 L of milk to take home at their initial visit. All subjects were provided with a measuring jug to measure 150 ml of milk, as well as sufficient kiwifruit and bananas to last until the next delivery. Bananas were packaged and delivered weekly to subjects and kiwifruit were delivered every 2 weeks to subjects by a courier company. Subjects were provided with guidelines for storing the cereal, milk and fruit. It was recommended that the bananas be stored at room temperature and the kiwifruit in the refrigerator. Common scenarios that could potentially arise during the 16 week intervention were explained. For example, if subjects missed breakfast it was recommended that breakfast be consumed later in the day and the time eaten recorded in the diary.

### Compliance diaries

Subjects were asked to maintain their normal daily routine, for example, eating patterns (apart from the breakfast), physical activity, and alcohol consumption or smoking habits for the duration of the study.

All subjects were asked to complete a compliance diary. They were asked to tick if they ate breakfast each day, and record the time the breakfast was eaten. They were asked to comment on any food not consumed including amounts, or any other food eaten with the breakfast or consumed within 1 hour either side of the breakfast.

On a weekly basis subjects were asked questions regarding illness, medication use, symptoms experienced (including abdominal discomfort, bloating, constipation, diarrhoea, nausea, vomiting, headache and fatigue), changes to their normal daily routine, supplement use, and whether they were experiencing any practical problems with eating the breakfast.

Subjects were telephoned at week 2, 4, 8 and 12 of the study to provide support and answer any questions. Two emails were sent to subjects over the course of the study to maintain subject motivation. It was emphasised to subjects to contact the researcher (by phone or email) if they experienced any problems during the 16 week intervention.

At the final appointment, subjects were asked to confirm whether there were any major changes to their lifestyle or health while undertaking the study, including questions on blood donation and supplement use.

### Subject evaluation of the breakfast

At their final appointment all subjects completed an evaluation questionnaire. Nine point hedonic scales (ranging from dislike extremely to like extremely) were used to determine the overall acceptability, appearance, flavour and texture of the breakfast cereal and fruit, and the overall acceptability of the milk [30]. A five point just right scale was used to determine whether the amount of cereal, fruit and milk provided were acceptable. Statements on the scale ranged from "too little" to "just right" to "too much" [30]. Subjects completed a food action rating scale (FACT) [31] asking whether they would eat the study breakfast in the future. This scale ranged from "I would eat this food every opportunity I had" through to "I would eat this only if I was forced to". Subjects were asked to comment on any problems they experienced with consuming the breakfast, the time taken to get used to consuming the study breakfast; any side effects experienced while completing the study (positive or negative), the impact of the breakfast on daily food intake and their intentions regarding future breakfast consumption. Subjects were also asked to comment on researcher support and whether they would take part in a similar study again.

### Data handling and statistical analysis

Statistical analysis will be performed using SPSS for Windows Version 16 (SPSS Inc., Chicago, IL, USA) [32]. Name and contact details of all subjects are stored in a database, in individual files and in Microsoft Excel. Data will be entered in to a single Microsoft Excel spreadsheet with subjects identified only by their unique study number. All entered data will be checked by another member of the research team to ensure it has been entered accurately prior to statistical analysis.

Descriptive statistics will be used to describe the baseline population using mean (standard deviation), median (25, 75 percentile) or frequencies summary statistics. Normality of distribution will be evaluated using the Kolmogorov-Smirnov test.

Non-normally distributed variables will be transformed into approximately normal distributions by logarithmic transformations and again tested for normality.

The main analysis will be the effect of the intervention on serum ferritin concentrations. Analysis of covariance will be used to compare the kiwifruit and the banana groups at the end of the study while controlling for baseline serum ferritin concentrations. Comparisons will also be made within the kiwifruit and banana groups between baseline and endpoint measures using the dependent t-test. The effect of the intervention on haemoglobin, soluble transferrin receptor, soluble transferrin receptor: serum ferritin ratio, ascorbic acid and carotenoids between and within groups will also be investigated using the statistical methods described above. The data will be investigated for possible confounding factors and effect modifiers e.g. age, body mass index, blood loss and dietary intakes. If confounding factors exist, analysis of covariance will be used to analyse the effect of the kiwifruit compared to the banana on iron status while controlling for the effects of these confounding factors. Serum ferritin, soluble transferrin receptor, soluble transferrin receptor: serum ferritin ratio and ascorbic acid will be tested using one-sided tests. Two sided tests will be used for all other variables. Effect size (to check for type 1 errors) will be calculated and where a statistically non-significant effect is seen, post hoc power calculations will be conducted to find out if the sample size was sufficiently large enough to detect an effect (to check for type 2 errors). Significance will be set at p < .05.

The percentage of days each subject consumed the breakfast will be calculated from compliance diaries. Descriptive statistics will be used to describe subject's evaluation regarding breakfast cereal, milk and fruit consumption.

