### Subjects

It was calculated that a minimum of 42 subjects with low iron stores would be required in each group to demonstrate a significant difference in serum ferritin of 2.5 μg/L at 80% power and 5% significance (two sided test). Power calculations were based on a standard deviation for serum ferritin of 4.1 μg/L (determined from a group of iron deficient women measured in our laboratory) (unpublished observation) and 2.5 μg/L was considered a possible clinically important difference. More subjects (n = 89) were recruited to allow for drop-outs from the study.

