### Randomisation of subjects

Eighty nine women were recruited to take part in the intervention phase of the study. Subjects were matched in pairs according to their serum ferritin level and age. Each subject was randomly allocated to either the kiwifruit group or banana group by a coin toss. Forty four women were allocated to the kiwifruit group and forty five women to the banana group.

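### Serum ferritin is planned with a two-sided 5% test but will be tested one-sided at p < .05, which doubles the chance of a false claim of benefit.

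*Protocol article*

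**What the plan says.** In the Protocol article, the Subjects section asks for at least 42 women per group. The target is a ferritin difference of 2.5 μg/L, and the error rates are specified as "at 80% power and 5% significance (two sided test"). The spread is also given there, in μg/L: "Power calculations were based on a standard deviation for serum ferritin of 4.1".

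The Data handling and statistical analysis section makes serum ferritin the main analysis, comparing the groups at the end of the study by analysis of covariance on baseline ferritin. The same paragraph then says: "Serum ferritin, soluble transferrin receptor, soluble transferrin receptor: serum ferritin ratio and ascorbic acid will be tested using one-sided tests". The next sentence is "Two sided tests will be used for all other variables". The section closes with a single threshold of p < .05 for everything.

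Neither section mentions the other's choice. No 2.5% level is attached to the one-sided tests, and no reason for using them is given.

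**The concern.** The number of women and the standard of proof for the main outcome come from different rules. A one-sided test at 5% asks for less evidence of benefit than the two-sided 5% test behind the sample size. A favourable ferritin result with a two-sided p-value between .05 and .10 would be non-significant under the Subjects section and significant under the analysis section. With both rules in print, either could be cited once the p-value is known.

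The article gives no case for ruling out the other direction. Its Background reports that earlier ascorbic acid studies found little or no effect on iron status, and it calls the effect on iron status over time unclear. A ferritin difference in favour of banana, however large, could not be declared under the one-sided rule.

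**Working it through.** **Inputs.** From the Subjects section: difference 2.5 μg/L, SD 4.1 μg/L, 80% power, 5% two-sided, 42 per group. From Randomisation of subjects: 44 and 45 women allocated. From the analysis section: one-sided test for ferritin, p < .05.

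**1. Reproduce the stated sample size.** Per group, n = 2 × [SD × (z_alpha + z_power) / difference]².

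- Two-sided 5%: 2 × [4.1 × (1.960 + 0.842) / 2.5]² = 42.2. This agrees with the stated 42; strict rounding up gives 43, and the t-distribution gives 44.
- One-sided 5%: 2 × [4.1 × (1.645 + 0.842) / 2.5]² = 33.3, so 34 (also 34 with the t-distribution).

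The stated 42 comes from a two-sided calculation, so the words in the Subjects section are not a slip.

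**2. False claim of benefit when there is no effect.**

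- Two-sided 5%: 5% / 2 = 2.5% in the kiwifruit direction.
- One-sided 5%: 5% in that direction.
- Ratio: 5 / 2.5 = 2.

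The total error rate is 5% in both cases.

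**3. Observed difference needed for significance.** With 42 per group, the standard error is 4.1 × √(2/42) = 0.895 μg/L, with 82 degrees of freedom.

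- Two-sided: 1.989 × 0.895 = 1.78 μg/L.
- One-sided: 1.664 × 0.895 = 1.49 μg/L.

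**4. Power for a true difference of 2.5 μg/L (noncentral t).**

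| Women per group | Two-sided 5% | One-sided 5% |
|---|---|---|
| 42 / 42 | 78.9% | 87.0% |
| 44 / 45 | 81.2% | 88.7% |

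**5. How often the choice of rule decides the result, at 42 per group.** With no true effect, a favourable result falls between the two thresholds in 5% − 2.5% = 2.5% of trials. With a true difference of 2.5 μg/L, it does so in about 87.0% − 78.9% = 8.1% of trials.

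Steps 3 to 5 use the unadjusted t-test that the Subjects inputs imply. The planned analysis adjusts for baseline ferritin and may be on a log scale, and the article does not give the baseline-to-endpoint correlation. The μg/L thresholds and the powers are therefore illustrative. Step 2 and the 2.5% in step 5 do not depend on those choices.

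**The case against.** The strongest defence is that the one-sided test is declared in advance and follows a directional hypothesis: the Background expects kiwifruit to enhance absorption and improve iron status. A trial sized two-sided can be analysed one-sided; it is then simply larger than that test needs. Readers can see the choice and convert the p-value. The overall type I error is not inflated, and only results with a two-sided p between .05 and .10 are affected.

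Much of this is fair. The two sections are not logically incompatible, and a prespecified one-sided test can be legitimate. Choosing sidedness variable by variable is not a contradiction either, so leaving haemoglobin two-sided is at most an unexplained choice. The directions for transferrin receptor and its ratio to ferritin can be inferred from the hypothesis, although the article does not state them.

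The defence still leaves the main point. The article nowhere says that the two-sided sizing was deliberate caution, and it gives no reason for treating an unfavourable ferritin difference as impossible or of no interest. Had it done so, the bar for claiming benefit would still be lower than the one on which the trial was designed.

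**Conclusion.** The concern holds. The main outcome is designed at two-sided 5% and analysed at one-sided 5%, without explanation. The probability of falsely claiming that kiwifruit raises ferritin is 5% instead of the 2.5% implied by the design. On the Subjects inputs, the difference that would count as significant is about 0.29 μg/L smaller (1.78 − 1.49).

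Two assumptions apply. The one-sided ferritin test is taken to favour kiwifruit, as the stated hypothesis implies. The μg/L and power figures are for an unadjusted comparison. The doubling needs only the first. Because the mismatch can decide whether the main result is called positive, it should be resolved before ferritin is analysed.

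**What to change.** In Data handling and statistical analysis, replace the one-sided sentence and the one after it with a single statement that all outcomes, including ferritin, transferrin receptor, the ratio and ascorbic acid, are tested two-sided at 5%. Give the ferritin difference with a two-sided 95% confidence interval so that the estimate and the test use the same standard.

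A one-sided test at 2.5% would keep the same error rate for a claim of benefit and is acceptable if the direction is stated for each variable. Keeping one-sided 5% would need a written justification and a matching statement in the Subjects section; it is the weaker option because the stated 42 was not derived that way.

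The cost is a change of wording. The section is written in the future tense, so the change can be made and dated before the analysis. No new data are needed. On the Subjects inputs, power goes from 88.7% to 81.2% at the 44 and 45 women randomised, or from 87.0% to 78.9% if only 42 per group finish. Both are about the 80% that was planned.

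### Effect size and post hoc power are assigned to check for type 1 and type 2 errors, and neither calculation can do that

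*Protocol article*

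**What the plan says.** In the protocol article, under Data handling and statistical analysis, the main analysis is an analysis of covariance of final serum ferritin, adjusted for baseline. Two checks follow. The first is "Effect size (to check for type 1 errors) will be calculated". The second applies where an effect is not significant: "post hoc power calculations will be conducted to find out if the sample size was sufficiently large enough to detect an effect", with the stated purpose "to check for type 2 errors". The threshold is given as "Significance will be set at p < .05", and on sidedness: "Serum ferritin, soluble transferrin receptor, soluble transferrin receptor: serum ferritin ratio and ascorbic acid will be tested using one-sided tests".

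Under Subjects, the sample size rests on a difference in serum ferritin of 2.5 μg/L, an SD of 4.1 μg/L, 80% power and a two-sided 5% test, giving "a minimum of 42 subjects with low iron stores would be required in each group". The 2.5 μg/L "was considered a possible clinically important difference". Under Randomisation of subjects, 44 women were allocated to kiwifruit and 45 to banana.

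The text does not name the effect to be put into the post hoc power calculation. It sets no power level for judging the answer.

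**The concern.** Both checks are given a purpose that they cannot fulfil. An effect size does not separate a true effect from a chance finding, because any result that reaches significance must show a sizeable standardised difference. Power calculated after the fact does not show whether a particular non-significant result is a type 2 error.

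What is at stake is the interpretation of a null primary result. That outcome is plausible: the Background describes earlier ascorbic acid studies that mostly failed to change iron status. The trial has a difference of interest against which a null result can be read. The stated check could bypass it and describe informative negative data as coming from too small a sample.

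**Working it through.** **Inputs.** Difference 2.5 μg/L, SD 4.1 μg/L, 42 per group, 80% power and two-sided 5% (Subjects); 44 and 45 randomised (Randomisation of subjects); one-sided test of ferritin at 0.05 (Data handling and statistical analysis).

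**1. The plan's own figure.** n = 2 × [4.1 × (1.960 + 0.842) / 2.5]² = 42.2 per group. The stated 42 reproduces, so the sample size is not in question.

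**2. Effect size as a check on type 1 error.** In an unadjusted comparison, the smallest standardised difference that can be significant is t_crit × √(1/44 + 1/45), and the square root is 0.212.
- One-sided: 1.663 × 0.212 = 0.35.
- Two-sided: 1.988 × 0.212 = 0.42.

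False positives clear this bar just as true positives do.

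**3. Post hoc power from the observed effect.** With z the observed statistic, one-sided power is Φ(z − 1.645), and two-sided power is Φ(z − 1.960) + Φ(−z − 1.960). Both depend on z alone, and hence on the p-value alone. A non-significant z lies below the critical value, so power is about 50% or less.

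| p-value | 0.05 | 0.10 | 0.20 | 0.50 |
|---|---|---|---|---|
| One-sided observed power | 50% | 36% | 21% | 5% |
| Two-sided observed power | 50% | 38% | 25% | 10% |

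**4. Illustration, 42 per group, unadjusted SD 4.1.**
- SE = 4.1 × √(2/42) = 0.895; the 95% half-width is 1.989 × 0.895 = 1.78.
- An estimate of 0.5 μg/L has a 95% interval of −1.28 to 2.28, which excludes 2.5.
- Here z = 0.5 / 0.895 = 0.56, so observed power is 9% two-sided or 14% one-sided.
- The upper limit stays below 2.5 for estimates up to 2.5 − 1.78 = 0.72.

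If the true difference is zero, the upper 95% limit falls below 2.5 in about 80% of trials with 42 per group, and in about 82% with 44 and 45 (SE 0.869; Φ((2.5 − 1.704)/0.869)).

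**5. Dependence on the SD.** The residual SD after adjustment for baseline is not given. With 42 per group the half-width is 1.989 × 0.218 × SD = 0.434 × SD. For assumed SDs of 3, 4.1, 5 and 6 it is 1.30, 1.78, 2.17 and 2.60. An estimate of 0.5 therefore excludes 2.5 only while the SD is below about 2.0 / 0.434 = 4.6. Step 3 does not depend on the SD.

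**6. Post hoc power from the planned effect.** With 2.5, SD 4.1 and 44 and 45 women, power is about 82% two-sided (81% by the t distribution) or 89% one-sided. This is the design calculation at the randomised numbers. It takes nothing from the observed difference.

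**The case against.** A reader might infer that under this plan every null result will be declared underpowered, so that the trial could never conclude that kiwifruit fails to raise ferritin by 2.5 μg/L. The document does not support that. It does not say that the observed effect will be used, and since 2.5 μg/L is the only difference of interest it names, the planned effect is an open reading. On that reading power is about 82%, and a null result would not be called underpowered. Nor does the plan set a power threshold or a rule by which low power overrides the result.

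It is also fair to say that the absence of a confidence interval, or of a rule for reading one, is detail that an article may leave to the full protocol or analysis plan. It is not counted as a fault here. The figures in the illustration use an unadjusted planning SD and are not a forecast.

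All of this stands. What it leaves intact is that the article states a purpose for each calculation, both purposes are wrong, and neither choice of effect repairs the second. With the effect unnamed, the answer can also turn on a choice made after the data are seen.

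**Conclusion.** The point holds as an error in stated method. Effect size cannot check for type 1 error, and this needs no assumption about how the plan is carried out. Post hoc power cannot check for type 2 error under either reading: from the observed effect it repeats the p-value and is about 50% or less for every non-significant result; from the planned effect it repeats the design.

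The practical harm, informative negative data read as an inadequate sample, is conditional. It requires that the observed effect be used and that low power be taken as a verdict on the sample. Its size, estimates up to about 0.7 μg/L, rests on SD 4.1 and 42 per group. The primary estimate and p-value are unaffected, so this is a change that should be made rather than a threat to the trial.

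**What to change.** Delete the post hoc power calculations and the phrase giving effect size the role of checking type 1 error. Report the baseline-adjusted difference in ferritin with its 95% confidence interval. For a non-significant primary result only, read the upper limit against 2.5 μg/L: if it is below 2.5, the effect of interest is excluded; otherwise the result is inconclusive.

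Two details must be settled with it.

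- **Sidedness.** The design is two-sided 5% ("serum ferritin of 2.5 μg/L at 80% power and 5% significance (two sided test"), while ferritin is to be tested one-sided. Reconcile these and make the interval match. Otherwise the two can disagree: at SE 0.895 an estimate of 1.6 gives t = 1.79 and one-sided p of about 0.04, yet its two-sided 95% interval is −0.18 to 3.38. If a one-sided 5% test is kept, the interval that agrees with it is a two-sided 90% interval.
- **Scale.** The plan log-transforms non-normal variables. A log analysis gives a ratio, which cannot be compared directly with 2.5 μg/L. Either express the margin on the log scale in advance or estimate the difference on the original scale.

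The cost is a few sentences. No further data or participants are needed, and the analysis work is no greater than that now planned.
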